## Materials and methods

### Study population

The [name] study (**M**u**s**cle mass in the **Li**fe and **L**ongevity **A**fter **C**ancer cohort) will include approximately 6000 postmenopausal women. Participants will be recruited from the ongoing Women’s Health Initiative (WHI) study cohort. The WHI is a prospective longitudinal study focused on examining causes of morbidity and mortality in postmenopausal women.

All [name] participants have been active participants in the WHI study since the 1990s. Postmenopausal women aged 50–79 years enrolled in the WHI clinical trials and observational study between 1993 and 1998 at 40 clinical centers across the U.S. (n = 161,808) [26]. Over the past thirty years, follow-up has been consistent and is still ongoing. In the initial phase of the WHI (up to 2005), participants visited clinical centers for in-person measurements, including anthropometric measurements. Since then, the WHI has collected comprehensive annual questionnaires on medical history, demographics, and lifestyle characteristics via mail, online surveys and telephone [27].

For [name], we will recruit women who are actively still participating in the WHI and have recently completed an in-home study funded by the WHI. The sample size for [name] is limited to all women who have completed the WHI home visit, as the home visit will provide important information on measured covariates (i.e., body weight, blood-based biomarkers, measures of physical function). The study population is depicted in Fig 1. Cancer survivors will be recruited from a WHI sub-cohort called the Life and Longevity After Cancer (LILAC) study. Postmenopausal women with no cancer history (“non-cancer controls”) will be recruited from a WHI sub-cohort called the Long Life Study 2 (LLS2), a minority enriched sub-cohort of women [28, 29]. The WHI is currently completing in-home study visits for LILAC and LLS2 participants. Home visits consist of anthropometric measures (e.g., height, weight, blood pressure), assessment of physical function via the short physical performance battery (SPPB), and a fasting venous blood draw [30].

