#### Statistical plan

*Aim 1*. We will create age-standardized muscle mass percentile curves to characterize the distribution of D_3_Cr muscle mass in cancer survivors and non-cancer controls. We hypothesize that cancer survivors will have lower muscle mass compared to age-matched cancer-free controls. We will also develop percentile curves for women from different racial/ethnic minority groups to examine potential differences in the distribution of muscle mass among Non-Hispanic White, Non-Hispanic Black, and Hispanic women. Additionally, to examine the effect of cancer-related variables on age-standardized muscle mass among cancer survivors, we will create percentile curves stratified by time since diagnosis and treatment modality (chemotherapy yes/no). These stratified analyses will specifically address questions regarding the effect of heterogeneity of cancer type and stage of cancer at diagnosis. According to guidance from the World Health Organization and U.S. Centers for Disease control, precision of estimates for growth curves depend on the number of participants at given percentile value [35–37]. The World Health Organization suggests adequate precision for growth curve modeling is achieved with a minimum of sample size of 200 participants per percentile [35]. Based on the planned recruitment of WHI participants, we will have adequate power for this analysis.

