*Aim 3*. We will draw on approximately 30 years of data from WHI study participants (~1993–2023) to examine the antecedents of low muscle mass in postmenopausal women. Our primary interest in this analysis is to predict risk of having low muscle mass, defined as <10^th^ percentile muscle mass for age. We will also conduct sensitivity analyses to examine risk of being <5^th^ percentile (very low muscle mass) and <25^th^ percentile (at risk for low muscle mass). Separate risk prediction algorithms will be created for cancer survivors and non-cancer controls, and we will stratify by race/ethnicity when creating the prediction equations. We will first use multivariable logistic regression to predict the risk of low muscle mass. After standardizing predictors, the regression parameters are easily interpreted as log-odds ratios and variable importance can be assessed by comparing the magnitude of the effects. To achieve a more parsimonious model, we will use least absolute shrinkage and selection operator (LASSO) logistic regression for variable selection [44]. This approach is one in which estimation of regression coefficients is achieved by maximizing the log-likelihood of the logistic regression model that includes all variables, subject to the condition that the sum of the absolute value of the effects is smaller than a specified value, referred to as a tuning parameter [44]. As a result, the regression coefficients are continuously shrunk so that important effects stay in the model while less desirable coefficients are shrunk to zero [44]. This continuous shrinkage process results in more stable predictions than subset selection methods such as backward selection.

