We will then examine whether using machine learning algorithms will improve predictive performance compared to standard approaches. The advantage of these approaches over logistic regression is that they allow for non-linear relationships between predictors and outcome and data-driven interactions that do not require a prior specification and may substantially improve predictive ability [45, 46]. Many approaches are available to analysts in standard statistical software. We propose to consider random forests [47], gradient boosting [48], and super learner [49]. Random forests and gradient boosting are ensemble methods based on building a large number of decision trees [47, 48]. In the random forest algorithm, many trees are built from resamples of the data with a random subset of the original predictors and are averaged to produce a single prediction model. In gradient boosting, a small tree is adaptively improved using resamples of the data. The super learner is an ensemble learning framework that combines predictions obtained from a range of algorithms/methods, each of which may be used to construct a prediction tool, to form a single overarching prediction tool [49]. Through theoretical work and simulations, the super learner framework has been shown to have optimal statistical properties, most notably that the final prediction tool outperforms or does no worse than any of the component algorithm/methods [49]. We will train the model on 80% of the data and validate on the remaining 20%, which is independent from the training data.

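### Aim 3: a 20% hold-out on a 10% outcome leaves about 60 validation events per survivorship group, too few to show modest gains from machine learning, and few in smaller race/ethnicity strata

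*Protocol article*

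**What the plan says.** Under Study population, the Protocol article states that the study "will include approximately 6000 postmenopausal women". Under Statistical plan, Aim 3 sets the outcome: "Our primary interest in this analysis is to predict risk of having low muscle mass, defined as <10^th^ percentile muscle mass for age". Sensitivity analyses use the 5th and 25th percentiles. The models are divided as follows: "Separate risk prediction algorithms will be created for cancer survivors and non-cancer controls, and we will stratify by race/ethnicity when creating the prediction equations". The race/ethnicity groups are named only under Aim 1: "Non-Hispanic White, Non-Hispanic Black, and Hispanic women".

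Logistic and LASSO regression come first. Random forests, gradient boosting and super learner are then examined to see whether they predict better. Validation is described in one sentence: "We will train the model on 80% of the data and validate on the remaining 20%, which is independent from the training data". No other validation of the models is described. The one statement on adequate numbers, 200 participants per percentile, concerns the Aim 1 curves, not Aim 3.

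**The concern.** The precision of a validation depends mainly on the number of events in the validation set, and here three choices reduce it. The outcome is about 10% by definition (5% in one sensitivity analysis), the cohort is divided by survivorship and then by race/ethnicity, and only a fifth of the women are used to assess performance. Four-fifths of a scarce event count therefore contribute nothing to the estimate of how well the algorithms work.

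Two results are at stake. One is the comparison the plan sets itself, machine learning against standard regression, where plausible gains may be small. The other is performance by race/ethnicity, where a wide interval could be misread as evidence that an equation works, or fails, in a minority group.

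**Working it through.** The article gives no event count, precision target or power for Aim 3, so there is no stated figure to reproduce.

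**Inputs from the article:** about 6000 women; outcome prevalence 10% (5% and 25% in sensitivity analyses); hold-out fraction 20%; separate survivor and control algorithms.

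**Assumptions, not in the article:** 3000 women per survivorship group (range 2000–4000); percentiles set within each group, so that prevalence is 10% in each; true AUC 0.75; correlation r between the AUC estimates of two algorithms scored on the same women of 0.5 to 0.9; stratum sizes of 300, 600 and 1000 as illustrations.

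**Step 1, events.** Validation events = n × 0.20 × prevalence. For 3000 women at 10%: 3000 × 0.20 × 0.10 = 60, with 540 non-events.

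**Step 2, precision of one AUC (Hanley–McNeil).** With A = 0.75, a = A/(2 − A) = 0.600 and b = 2A²/(1 + A) = 0.643:

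SE² = [A(1 − A) + (n₁ − 1)(a − A²) + (n₀ − 1)(b − A²)] / (n₁n₀)

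For n₁ = 60 and n₀ = 540: (0.1875 + 59 × 0.0375 + 539 × 0.0804) / 32400 ≈ 0.00141. SE = 0.0376 and half-width = 1.96 × 0.0376 = 0.074.

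| Validation set | Events | AUC 95% half-width |
|---|---|---|
| Group, 10th percentile | 60 (40–80) | 0.074 (0.090–0.064) |
| Group, 5th percentile | 30 (20–40) | 0.103 (0.126–0.089) |
| Group, 25th percentile | 150 (100–200) | 0.049 (0.060–0.042) |
| Stratum of 1000, 10th percentile | 20 | 0.13 |
| Stratum of 600, 10th percentile | 12 | 0.165 |
| Stratum of 300, 10th percentile | 6 | 0.234 |

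Bracketed ranges are for groups of 2000 to 4000 women. The choice of AUC matters little: with 60 events the half-width is 0.077 at an AUC of 0.70 and 0.069 at 0.80.

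**Step 3, comparing two algorithms.** Smallest paired difference detectable with 80% power at two-sided 0.05 = (1.96 + 0.84) × SE × √[2(1 − r)]. With 60 events: 0.105 at r = 0.5, 0.067 at r = 0.8 and 0.047 at r = 0.9. With 6 events: 0.212 at r = 0.8 and 0.150 at r = 0.9.

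**Step 4, the same women under resampling.** If out-of-sample predictions for all women are treated as one sample, which is optimistic, a group of 3000 has 300 events. The half-width is then about 0.033, and the detectable difference 0.047, 0.030 and 0.021 at r = 0.5, 0.8 and 0.9. A stratum of 300 has 30 events and a half-width of about 0.104.

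**The case against.** A reader might infer that so few events remain that the models cannot be validated or ranked at all. The documents do not support that. At the level the text clearly requires, one algorithm for survivors and one for controls, about 60 events give an imprecise but usable estimate, and the 25th-percentile analysis has about 150. Very low counts arise only in small strata whose sizes the article does not give. The control cohort is described as minority enriched, so its strata may be nearer the upper end of the illustrated range.

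The text also does not say whether the split is made once or repeated, or whether it is made overall or inside each stratum. Stratifying by race/ethnicity most naturally suggests separate equations, but not necessarily separate hold-outs. Nor does it name the reference population for the percentiles. If survivors were classified against a common or control reference and had lower muscle mass, as hypothesised, they would have more than 10% events.

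A reader might further infer that the best algorithm will be picked on the hold-out and its performance overstated. The article does not say so. It calls the hold-out independent of the training data, and super learner combines algorithms without needing a winner. Tuning and performance measures may properly be left to a fuller document.

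These points limit the concern to precision and make the stratum figures conditional. They do not remove it, because the 20% hold-out is a stated choice and its cost in events follows directly.

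**Conclusion.** The concern holds as one of inefficient validation. Under the assumptions listed, a hold-out of about 60 events per group can reliably detect AUC differences of only about 0.05–0.10, so whether machine learning improves prediction would be poorly answered for any smaller gain. The 5th-percentile analysis is weaker (about 30 events, half-width 0.10); the 25th is adequate for a single AUC (0.05).

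If validation is done within race/ethnicity strata, a stratum of 300–1000 women gives half-widths of 0.23–0.13. At 300 women, an AUC of 0.75 would carry an interval from about 0.52 to 0.98. The group-level conclusion holds across 2000–4000 women per group; the stratum-level conclusion depends on counts the article does not report. This should be changed, but it does not undermine the study, since it affects one of three aims and needs no new data.

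**What to change.** Replace the 80/20 hold-out with repeated nested k-fold cross-validation, with all tuning inside the folds, or with bootstrap optimism correction, using all women in each survivorship group. Apply the same resampling to every algorithm so that comparisons are paired. Report AUC and calibration overall and by race/ethnicity from the out-of-sample predictions, with intervals. State the expected number of events per group and per stratum once recruitment counts are known.

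Resampling does not rescue small strata (about ±0.10 at 300 women), so performance there should be labelled exploratory. The planned stratification by race/ethnicity is an explicit design choice and can stay; this point does not require pooling.

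The cost is a change of wording, more computing, and intervals that need a resampling variance.

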## Discussion

The remote collection of D_3_Cr muscle mass has the potential to transform our understanding of the antecedents and consequences of low muscle mass in older adults. The D_3_Cr method is a simple, inexpensive, and non-invasive assessment of muscle mass that can be used to measure muscle mass at home. This approach maximizes scientific rigor while minimizing participant burden. To our knowledge, this will be the first large-scale epidemiologic study to measure total body skeletal muscle mass remotely in older women using D_3_Cr. [name] is well-positioned to address key unanswered questions about muscle mass in older and long-term postmenopausal cancer survivors. The WHI is the ideal setting for this study because the nested sub-cohorts (LILAC and LLS2) allow us to estimate the extent to which outcomes (i.e., decline in physical function) are specifically related to cancer or attributable to other factors. In addition, all participants recently completed a home visit funded by the WHI contract. Establishing a valid non-cancer comparison group is often a challenge in the context of cancer research; in [name], both cancer survivors and non-cancer controls are drawn from the same source population (WHI). This will create comparability across groups.

Avenues for future work with D_3_Cr could include its use as either an exposure (i.e., examining the relationship of D3Cr with a particular health outcome) or outcome (i.e., examining the effect of an intervention or treatment on change in D3Cr muscle mass). In particular, broadening the use of D_3_Cr has significant potential to inform the development of targeted intervention programs for older adults. As one example, D_3_Cr could be used as an outcome variable in a randomized clinical trials of a physical activity and/or dietary intervention. Successful interventions to increase muscle mass in older adults could improve quality of life, decreasing acute and chronic disease outcomes, and promoting more effective resource utilization. Future work could also examine the use of D_3_Cr in screening intervention programs in routine clinical practice (e.g., during annual physical examinations).

As with any study protocol involving primary data collection, potential problems may arise. Investigators using the D_3_Cr protocol must carefully consider alternative strategies should they be necessary. Participant non-response and loss-to-follow-up are concerns in any prospective study design, especially in older adults. The WHI has a long history of exceptional follow-up and participant retention, including a very small proportion of loss-to-follow-up. Despite the success of sample return in our pilot study, we anticipate some participants will not collect the urine sample or send it back during the required time frame. Also, in our experience, it can be confusing to schedule a pickup by telephone because automatic voice-prompt software may be challenging to navigate. We will provide participants with a pre-addressed return mailing label and extremely detailed, step-by-step written instructions as we did successfully in the pilot study. We will use a large type font (size 14) for all instructions and mailings in case there are participants with poor eyesight. If a participant is having a difficult time scheduling the sample pick up, we will instruct them to call the study team and we will schedule the pick-up for them. Importantly, in our pilot study, nearly all participants successfully called to schedule a pick up; only 2 women required assistance from the WHI Buffalo clinic staff to schedule the pickup.

The D_3_Cr method has the potential to create a new area of scientific inquiry and significantly advance our understanding of muscle mass in the context of aging and cancer research. The remote D_3_Cr measurement approach developed in [name] broad applications across epidemiology, public health, and clinical medicine. Sharing the [name] study protocol will make this approach more accessible to researchers in a wide range of contexts.
